## Methods

The ERTAAD is an observational registry including patients who underwent surgery for acute TAAD at 19 centers of cardiac surgery located in seven European countries (Belgium, Czech Republic, Finland, France, Germany, Italy and the United Kingdom) (Table 1) from January 1, 2005 to March 31, 2021. Data will be retrospectively collected on patients treated during the study period and the aim is to gather further data for future clinical research on this topic. Data on consecutive patients with acute TAAD will be collected into a Microsoft Access datasheet (Redmond, Washington, USA) with pre-specified baseline, operative and outcome variables. Permission to conduct this study will be requested from institutional or national review boards according to local legislation.

**Table 1 Tab1:** Participating centers

Participating centers	
1. Ziekenhuis Oost-Limburg, Genk, Belgium	
2. Saint-Luc’s Hospital, Brussels, Belgium	
3. Sint-Jan Hospital, Bruges, Belgium	
4. Antwerp University Hospital, Edegem, Belgium	
5. University Hospitals Leuven, Leuven, Belgium	
6. Institute of Clinical and Experimental Medicine, Prague, Czech Republic	
7. Helsinki University Hospital, Helsinki, Finland	
8. Jean Minjoz University Hospital, Besançon, France	
9. Hôpital Henri Mondor, Assistance Publique - Hôpitaux de Paris, Créteil, France	
10. Leipzig Heart Center, Leipzig, Germany	
11. University Heart and Vascular Centre Hamburg, Hamburg, Germany	
12. Münster University Hospital, Münster, Germany	
13. University of Turin, Turin, Italy	
14. University of Verona Medical School, Verona, Italy	
15. University of Udine, Udine, Italy	
16. Glenfield Hospital, University Hospitals of Leicester, Leicester, UK	
17. Liverpool Heart and Chest Hospital, Liverpool, UK	
18. Sheffield Teaching Hospital, Sheffield, UK	
19. Southampton University Hospital, Southampton, UK	

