## Sample size calculation

The impact of total aortic arch repair compared to more limited aortic resection on the early and late outcomes will be one of the main topics of research from this registry. Therefore, in the light of the expected limited frequency of this surgical strategy, we performed a sample size analysis considering the extent of distal aortic resection. Despite the limitation of a pooled analysis which did not take in to account the cumulative incidences from competing risk analysis and the segment of repeat operation, Poon et al. [23] estimated a pooled hazard ratio on 0.73 (95%CI 0.56–1.18) of freedom from any late aortic reoperation for total arch replacement. Based on this hazard ratio, a sample size of 163 patients per study groups would be enough to reject the null hypothesis (alpha 0.05, power 0.80). Pan et al. [24] reported a freedom from distal reoperation after ascending aortic resection at 8 years of 95.3% which was not statistically different from that of hemiarch or total aortic arch repair (92.4%, *p* = 0.22). For the sample size calculation of a non-inferiority trial, we assumed a freedom rate from distal aortic reoperation of 95% and we considered that a difference in the reoperation rate as large as 10% in favor of a total aortic arch repair still allow the less extensive repair to be non-inferior (delta = 0.1, power 0.90, one-sided confidence 97.5%), the required sample size would be 100 patients per each group. We assume that about 5% of patients have undergone total arch repair in this collaborative registry and therefore a study population of 4000 patients would be enough to investigate the impact of total aortic arch repair in preventing late aortic reoperation in patients with acute TAAD. The participating hospitals are expected to provide a sample size of more than 6000 patients (i.e. at least a mean of > 20 procedures for acute TAAD each year), which would prevent a type II error.

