Logistic and linear regression analyses will be employed to identify independent risk factors for early adverse events with and without a stepwise approach. For the purpose of developing a risk scoring method from this registry, the study cohort will be randomly divided into two datasets, i.e. the derivation data set (75.0% of patients) and the validation data set (25.0% of patients). Univariate analysis will be performed on all candidate covariates of the derivation dataset to identify predictors of in-hospital mortality. Multiple logistic regression analysis will be then performed using the derivation dataset. A stepwise procedure with a bootstrap approach will be used, and 100 samples will be extracted with a size of 70% of the derivation dataset. A stepwise procedure will be applied to each sample (probability to stay = 0.05; probability to entry = 0.1). Variables selected in at least 50% of the stepwise procedures will be included in the regression model. Additional covariates were selected using a forward selection comparing the Akaike information criterion for the models with and without each covariate. The model with the lowest Akaike information criterion will be selected for each forward step, until the inclusion of a new covariate determined an increase in the Akaike information criterion value. The model will be tested in the validation data set for calibration, using the Hosmer–Lemeshow test, and for discrimination using the receiver-operating characteristic curve analysis. A comparison of the predictive ability of the new score with the current risk scoring methods for prediction of in-hospital mortality will be performed in the overall dataset as well as in the validation dataset using the DeLong test. The improvement of discrimination of the new score will be estimated by calculating the net reclassification index and the integrated discrimination improvement. Finally, to evaluate the adaptability of the new score for prediction of late mortality, Kaplan–Meier curves stratified by deciles of the new score will be plotted.

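### The only calibration check named for the new mortality score is the Hosmer-Lemeshow test, which gives no estimate and cannot exclude mild to moderate miscalibration

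*Protocol article*

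**What the plan says.** The Statistical analysis section of the Protocol article describes the risk score in some detail. The cohort is split at random into "the derivation data set (75.0% of patients) and the validation data set (25.0% of patients". Predictors of in-hospital mortality are chosen by univariate screening, bootstrapped stepwise selection and forward addition by the Akaike criterion. On calibration there is one statement: "The model will be tested in the validation data set for calibration", with the Hosmer-Lemeshow test as the method. The general significance level in the same section is 0.05.

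No other analysis named there measures calibration of this score:
- The ROC curve, the DeLong test, the net reclassification index and the integrated discrimination improvement concern discrimination or reclassification.
- The Kaplan-Meier curves by score decile concern late mortality.
- The observed/expected ratio in the paragraph on differences between institutions serves to compare centres.

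**The concern.** A mortality score is used for the risk it predicts, so a reader needs to know how far predicted and observed risk differ, and in which direction. The p-value of a goodness-of-fit test answers neither question, and failure to reject is not evidence of good calibration.

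Data-driven selection of predictors can also make predictions too extreme, which shows as a calibration slope below 1. If the test has little power against modest departures of this kind, the publication could report a non-significant result for a score whose risks are somewhat off, and no reader could tell. The article also leaves the degrees of freedom open, and in a validation set this changes the error rate of the test.

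**Working it through.** **Inputs from the article**
- Registry size: "The participating hospitals are expected to provide a sample size of more than 6000 patients" (Sample size calculation). This agrees with its own components: "19 centers of cardiac surgery located in seven European countries", "from January 1, 2005 to March 31, 2021" (16.25 years) and "at least a mean of > 20 procedures for acute TAAD each year" give 19 × 16.25 × 20 = 6,175.
- Validation set: 0.25 × 6,000 = 1,500.
- Mortality: 17%. Background cites 30-day figures of 16.9% to 18%, used here as a proxy for in-hospital death. Expected deaths: 0.17 × 1,500 = 255.
- Significance level: 0.05.

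**Assumptions, because the article gives no figure**
- Ten risk groups.
- A normally distributed predicted linear predictor with SD 1. As a sensitivity range, true AUC is set to 0.70, 0.75 and 0.80.

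**Statistic.** HL = Σ (O − E)² / [E(1 − E/n)] over the ten groups. For a model fitted on other data the reference distribution is chi-square with 10 degrees of freedom.

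**Simulated power, n = 1,500, 17% events**

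| True slope | HL, 10 df, SD 1 | HL, 10 df, AUC 0.70–0.80 | Test of slope = 1, SD 1 |
|---|---|---|---|
| 0.90 | 14% | 10–18% | 25% |
| 0.85 | 21% | 19–37% | 45% |
| 0.80 | 38% | 32–68% | 68% |
| 0.70 | 78% | 85–99% | 97% |

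The two HL columns differ because the first fixes the spread of the predictions and the second fixes the spread of true risk.

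**Overall shift, slope 1, HL on 10 df.** With observed odds 16% above predicted (SD 1), power is about 29%. Over AUC 0.70–0.80 it is:
- 14–17% at an observed/expected ratio (O/E) of 0.90, and 20–24% at 1.10
- 42–49% at 0.85, and 61–68% at 1.20
- 81–90% at 0.80, and 81–89% at 1.25

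With slope 0.80 combined with O/E 0.85 or 1.20, power is 78–96%.

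**Type I error.** It is about 5% on 10 degrees of freedom. On 8, the customary number for data to which the model was fitted, it is about 11% (9–13% over the AUC range). The higher power on 8 degrees of freedom (47–78% at slope 0.80) is partly bought by this excess.

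**Smaller set.** The article calls 4,000 patients enough for the arch question. The validation set would then be 1,000, with HL power of 28–51% at slope 0.80 and 64–92% at 0.70.

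**What estimation would give at n = 1,500**
- Slope: SE about 0.084 at a true slope of 1 (SD 1), so the 95% interval is ±1.96 × 0.084 = ±0.16. Over the AUC range the SE is 0.07 to 0.10.
- O/E: SE of log(O/E) ≈ √[(1 − 0.17)/255] = 0.057. Then 1.96 × 0.057 = 0.11, or about ±11%.
- The slope test has only about 5% power against a uniform shift, so the intercept or O/E must accompany the slope.

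**The case against.** **Larger errors are found.** A reader might infer that the test usually misses any miscalibration that matters at this sample size. The figures do not support that. Slope 0.70, O/E 0.80 or 1.25, and combined errors are detected in roughly 78% to 99% of runs. This part of the objection stands, and the point is limited to mild and moderate errors.

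**Heavy overfitting is not established.** A reader might also infer that the check would pass most overfitted scores. That would need slopes of 0.80 to 0.85 to be typical here, and nothing in the article shows it. The derivation set has about 0.75 × 6,000 = 4,500 patients and 0.17 × 4,500 = 765 deaths. A simplified simulation of selection at that size (SD 1) gave mean slopes of 0.94 with 40 candidates and 0.91 with 60. The slope fell below 0.85 in about 2% and 7% of runs. The article does not give the number of candidates, so this is only indicative, but the inference is not supported.

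**The slope test also lacks power.** At a slope of 0.85 it has about 45%. This is correct: the main gain is an estimate with an interval, and the extra power is secondary.

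**The registry may be larger.** Discussion gives at least 25 procedures per centre per year: 19 × 16.25 × 25 ≈ 7,700, or about 1,930 for validation. Power would rise, but slowly for mild errors. Going from 1,000 to 1,500 patients moves it only from 16–30% to 19–37% at slope 0.85.

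**The article is condensed, and group counts could be shown.** A fuller plan may add calibration measures, and observed and expected counts per group would show direction and size. The article promises neither. It does state a method, and that method is weak as stated.

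**Conclusion.** The point holds in limited form. The article fixes a single calibration method for the new score, and that method yields a p-value without an estimate. With about 1,500 validation patients, a non-significant result leaves mild to moderate miscalibration open: power is about 14%, 21% and 38% at slopes 0.90, 0.85 and 0.80, and about 29% for observed odds 16% above predicted. Gross miscalibration would usually be seen. With 8 degrees of freedom the test would also reject a well-calibrated score about twice as often as the nominal 5%.

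That the p-value carries no size or direction needs no assumption. The power figures rest on 17% in-hospital mortality, ten groups and an assumed spread of risk; the AUC range shows how far they move. The score is not among the outcomes listed in the abstract, and no comparison of surgical strategies depends on it, so the consequence is confined to how the score is validated and reported.

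**What to change.** In the risk-score paragraph of Statistical analysis, make the calibration assessment the calibration intercept (or observed/expected ratio) and the calibration slope, each with a 95% confidence interval, together with a smoothed calibration plot, all in the validation set. The Hosmer-Lemeshow test may stay as a secondary result, with 10 degrees of freedom stated for ten groups.

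Do not add a rule that shrinks the score whenever the validation slope is below 1. A well-calibrated score falls below 1 about half the time by chance. Using that slope to change the score would also turn the validation set into training data and leave the revised score without independent validation.

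The cost is about one sentence and a little extra analysis work. No new data are needed.

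### The DeLong comparison of the new risk score with existing scores in the overall dataset is optimistically biased, because 75% of that dataset built the new score; only the validation-set comparison supports inference.

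*Protocol article*

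**What the plan says.** All of this stands in the Protocol article, section Statistical analysis, in the paragraph on the risk score.

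- **Split.** The cohort is divided at random into "the derivation data set (75.0% of patients) and the validation data set (25.0% of patients").
- **Building.** Univariate screening is done on the derivation set. "Multiple logistic regression analysis will be then performed using the derivation dataset". For the stepwise selection, "100 samples will be extracted with a size of 70% of the derivation dataset". A forward step on the Akaike criterion then adds further covariates.
- **Testing the model itself.** "The model will be tested in the validation data set for calibration, using the Hosmer–Lemeshow test, and for discrimination" by ROC analysis. Only the held-out quarter is named here.
- **Comparison with current scores.** This "will be performed in the overall dataset as well as in the validation dataset using the DeLong test". Neither dataset is given priority, and no correction for optimism is mentioned.
- **Reclassification.** Improvement is also to be measured by "calculating the net reclassification index and the integrated discrimination improvement". The sentence names no dataset.
- **Late mortality.** Kaplan–Meier "curves stratified by deciles of the new score will be plotted". The time origin, the population and the dataset are not given.

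**The concern.** In the overall dataset the two sides of the comparison are treated differently. The new score's variables and coefficients were chosen to suit three quarters of the patients on whom it is judged. The existing scores were not tuned to this split. The new score therefore starts with an advantage unrelated to how it would perform in new patients.

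The DeLong test takes both scores as fixed in advance. Its variance contains nothing for selection and fitting on the same patients, so the 0.05 threshold does not hold its nominal error there. A large registry does not protect against this: the standard error becomes small enough for a modest bias in AUC to look significant.

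With no primary comparison named, a significant overall-dataset p-value could be reported as superiority over current scores even if the held-out comparison shows nothing.

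**Working it through.** **Inputs from the Protocol article.** Split 75.0% / 25.0%; more than 6000 patients expected (Sample size calculation); significance at p < 0.05 (Statistical analysis); 30-day mortality of 17% in one cited database (Background), used as a proxy for in-hospital mortality.

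**Assumptions not in the article.** Two-sided testing, so 2.5% in favour of the new score; 20 to 80 candidate covariates, 12 of them true predictors; true AUC about 0.70 in the closest imitation of the plan; an existing score with the same true AUC as the new one, not fitted to these patients; the Akaike step done on the derivation set, which is the natural reading.

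**Step 1: composition of the overall dataset.**
- Derivation: 0.75 × 6000 = 4500 patients; 4500 × 0.17 = 765 deaths.
- Validation: 0.25 × 6000 = 1500 patients; 1500 × 0.17 = 255 deaths.

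The article gives no sample size or power for the score comparison, so it has no figure of its own to reproduce.

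**Step 2: closest imitation of the planned procedure.** Univariate screen, resampled backward selection kept at 50% or more, Akaike forward step, fit on 75%, then DeLong. It used 20 resamples instead of 100; simulated mortality was about 16%.

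| | 40 candidates (150 runs) | 80 candidates (60 runs) |
|---|---|---|
| AUC excess of new score, derivation | 0.0161 | 0.0233 |
| AUC excess, validation | 0.0006 | −0.0037 |
| AUC excess, overall | 0.0123 | 0.0166 |
| New minus existing, overall (truth 0) | 0.0107 | 0.0190 |
| SE of difference, overall | 0.0036 | 0.0048 |
| New score falsely better, overall | 80% | 97% |
| New minus existing, validation | 0.000 | −0.0005 |
| SE of difference, validation | 0.0073 | 0.0097 |
| New score falsely better, validation | 2% | 5% |

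The overall excess is close to the weighted mean of the two parts: 0.75 × 0.0161 + 0.25 × 0.0006 = 0.0122, and 0.75 × 0.0233 − 0.25 × 0.0037 = 0.0166. The existing score was never falsely declared better in the overall dataset.

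**Step 3: other simulated settings at 6000 patients.**
- Selection at p < 0.157, 40 and 80 candidates: gain 0.0106 and 0.0191; false superiority 85% and 99%.
- A further run with a correlated existing score: gain 0.006 to 0.011; false superiority 44% to 88% overall, 2% to 6% in the validation set.
- A rough check with 25 runs per setting: AUC inflation about 0.005 with 20 candidates, and about 0.006 with 40 candidates and selection at p < 0.05.

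**Step 4: a less correlated existing score.** Lower correlation raises the standard error of the difference, so the same bias counts for less. By normal approximation, false superiority = P(Z > 1.96 − bias/SE), with an assumed SE of 0.009 to 0.012:
- 0.005 / 0.009 = 0.56, giving about 8%.
- 0.011 / 0.012 = 0.92, giving about 15%.
- 0.019 / 0.009 = 2.11, giving about 56%.

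For the smallest bias with a small standard error, 0.005 / 0.004 = 1.25 gives about 24%. The lower end of the range for a highly correlated score is therefore soft.

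**Step 5: cost of using held-out data only.** 0.0073 / 0.0036 and 0.0097 / 0.0048 are both about 2.0, as expected from a quarter of the patients (√4 = 2).

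**The case against.** The strongest reply is that the sound comparison is already planned. The same sentence specifies the validation set, and calibration and discrimination of the model are tested only there. Readers would see the optimistic and the held-out results side by side. This stands, and it confines the fault to the overall-dataset test and the missing priority between the two. A reader might infer that the comparison as a whole is rigged; the article does not support that, since it states the held-out comparison openly and gives no sign of intent.

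Two further inferences go beyond the text. One is that the reclassification measures will be computed in the overall dataset; the article names no dataset for them. The other is that the late-mortality curves contain the in-hospital deaths to which the score was fitted. That holds only if they start at surgery, which is not stated, and the Abstract lists in-hospital and late mortality as separate outcomes. No test is attached to these curves. Both points can only be conditional.

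The size is also open to challenge. The article gives neither the number of candidate covariates nor the existing scores, and false superiority near 99% needs many candidates and a highly correlated existing score. This stands as well, so the full range has to be given. Finally, the score is one product of the registry: the primary outcomes and the arch-repair sample size are unaffected.

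**Conclusion.** The point holds for the overall-dataset comparison. It is a stated analysis whose test is invalid, not a detail left to another document. With scores of equal true AUC, the spurious gain is about 0.005 to 0.019. The new score is falsely declared better in about 40% to 99% of simulated trials with a highly correlated existing score, and in roughly 8% to 55% with a less correlated one, against a nominal 2.5%. The validation-set comparison gave 2% to 6% and no material bias.

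The magnitudes rest on the assumed candidate count, selection threshold, number of true predictors and correlation between scores. The direction does not: fitting on the patients used for judging favours the fitted score. The bias is modest in AUC units but large against a standard error of 0.004 to 0.005. The conclusion does not extend to the validation-set comparison, nor, without further information, to the reclassification measures or the late-mortality curves.

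**What to change.** 1. State that the DeLong comparison in the validation set is the only inferential one, and compute the net reclassification index and integrated discrimination improvement there too.
2. Report any overall-dataset AUC of the new score as apparent performance without a p-value, or correct it for optimism by a bootstrap that repeats the full selection and fitting in each resample.
3. State the time origin and population of the late-mortality curves. If they were meant to start at surgery, draw them in hospital survivors instead, so that the in-hospital deaths used to fit the score do not create the separation.

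**Cost.** Wording, some computing time if the bootstrap is used, and no new data. The standard error of the AUC difference is about twice that in the overall dataset (0.007 to 0.010 against 0.004 to 0.005 in the simulations), so a small true gain is harder to show, and the reported gain will be slightly less favourable.

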## Discussion

### Implications for the treatment of TAAD patients

Analysis of the data from this collaborative registry will allow analysis of contemporary results of a large number of TAAD patients with a rather long follow-up period. We expect that the multicentre nature of this registry will allow reduction in the risk of bias related to institutional volume and surgical experience. In fact, all the participating centers have an annually rate of at least 25 procedures for acute TAAD and have an aortic surgery program which would facilitate an adequate follow-up and management of possible late aortic events after primary repair of TAAD. Therefore, we expect to gather data which will provide important insights into the assessment of the operative risk of patients with acute TAAD and conclusive results on the value of different surgical and perfusion strategies for this emergency condition.

### Limitations

The retrospective nature is the main limitation of this registry. However, our aim is to investigate the outcome at 15 years of these patients, and this may not be feasible with a prospective registry. Second, the prognostic impact of different treatment strategies will be analyzed using several statistical methods to adjust for baseline differences. However, the lack of randomization does not prevent the effects of confounding variables. Third, perioperative care may significantly vary between institutions as well as individual surgeons and their effects should be considered in all analyses.

